## Abstract

**Introduction:**

Paediatric heart transplant patients are disproportionately affected by Epstein-Barr virus (EBV)-related post-transplant lymphoproliferative disease (PTLD) compared with other childhood solid organ recipients. The drivers for this disparity remain poorly understood. A potential risk factor within this cohort is the routine surgical removal of the thymus—a gland critical for the normal development of T-lymphocyte-mediated antiviral immunity—in early life, which does not occur in other solid organ transplant recipients. Our study aims to describe the key immunological differences associated with early thymectomy, its impact on the temporal immune response to EBV infection and subsequent risk of PTLD.

**Methods and analysis:**

Prospective and sequential immune monitoring will be performed for 34 heart transplant recipients and 6 renal transplant patients (aged 0–18 years), stratified into early (<1 year), late (>1 year) and non-thymectomy groups. Peripheral blood samples and clinical data will be taken before transplant and at 3, 6, 12 and 24 months post-transplant. Single cell analysis of circulating immune cells and enumeration of EBV-specific T-lymphocytes will be performed using high-dimensional spectral flow cytometry with peptide-Major Histocompatibilty Complex (pMHC) I/II tetramer assay, respectively. The functional status of EBV-specific T-lymphocytes, along with EBV antibodies and viral load will be monitored at each of the predefined study time points.

**Ethics and dissemination:**

Ethical approval for this study has been obtained from the North of Scotland Research Ethics Committee. The results will be disseminated through publications in peer-reviewed journals, presentations at scientific conferences and patient-centred forums, including social media.

**Trial registration number:**

ISRCTN10096625.

STRENGTHS AND LIMITATIONS OF THIS STUDYThis is the first prospective study to monitor the temporal immune response to Epstein-Barr virus (EBV) infection within a group of patients known to be at a high risk of developing post-transplant lymphoproliferative disease.The integration of data from clinical parameters, in-depth immunophenotyping and EBV-specific T-lymphocyte functional assay permits robust analysis of potential predictive immune biomarkers.The multicentre study design optimises recruitment of participants.The primary study limitation is the low incidence of paediatric heart transplantation, which may affect the rate of study recruitment.

## Introduction

Post-transplant lymphoproliferative disease (PTLD) is the most common childhood cancer in paediatric recipients of a solid organ transplant. This heterogeneous group of life-threatening lymphoid malignancies is typically driven by Epstein-Barr virus (EBV) infection.^1^ PTLD comprises a histological spectrum that ranges from indolent non-destructive B-cell lymphoid infiltrates through to more aggressive and destructive polyclonal or monoclonal B-cell lymphomas, for example, Burkitt lymphoma and diffuse large B-cell lymphoma. These destructive PTLD subtypes are indistinguishable from high-grade mature B-cell lymphomas seen in immunocompetent children.^2^ Their incidence is allograft-dependent and ranges from 1%–2% in renal transplant recipients to as high as 10%–15% in heart transplant patients.^1 3^

PTLD has one of the worst clinical outcomes among childhood lymphomas. The estimated 2-year event-free survival (EFS) is 70% compared with 94% in sporadic cases within the general paediatric population.^4–6^ In even starker contrast is the survival outcome for paediatric heart transplant patients, who ostensibly have an inferior EFS compared with other non-cardiac organ transplants.^7 8^ The reasons for this potential disparity are still poorly understood, although partly ascribed to a higher incidence of therapeutic complications from organ rejection and treatment-related toxicities.^9^

The pathogenesis of PTLD is complex and multifactorial. It involves the interplay between EBV-driven lymphoproliferation, iatrogenic immunosuppression and the suspected functional exhaustion of T-lymphocytes due to graft-initiated chronic antigen stimulation.^10^ The role of EBV is clearly established in children, many of whom experience primary infection from an EBV-mismatched organ.^1 3 4^ In vitro and in vivo studies focused mainly on adult monomorphic PTLD have demonstrated distinct patterns of viral protein expression in infected B-lymphocytes.^10 11^ These expression patterns likely influence both the cellular composition of the tumour immune microenvironment and aberrant immune signalling, which result in immune escape of tumour cells.^10^

In paediatric heart transplant patients, cardiac surgery via median sternotomy in early childhood often requires routine thymectomy in order to access the heart and great vessels. Our earlier study retrospectively examined risk factors for PTLD in the largest UK cohort of paediatric orthotopic heart transplant patients to date.^3^ The risk of PTLD was found to be significantly higher in children with congenital heart disease (CHD) (HR=3.2; 95% CI=1.4 to 7.4) and early thymectomy in infancy (HR=2.7; 95% CI=1.3 to 5.2).^3^ Furthermore, children with CHD had persistently lower T-lymphocyte counts compared with children transplanted for acquired cardiomyopathy (CD4+: 430 cell/μL vs 963 cells/μL, p<0.01 and CD8+: 367 cells/μL vs 765 cells/μL, p<0.01).^3^ Similar studies have identified marked phenotypic and functional disruptions to the T-lymphocyte compartment in paediatric heart transplant patients compared with children receiving a liver or kidney transplant.^12 13^

During the first year of life, the thymus plays a crucial role in the development of cell-mediated immunity, providing a microenvironment for precursor T-lymphocytes to proliferate and differentiate into mature (naïve) T-lymphocytes.^14^ While it has been shown that neonatal thymectomy alone is associated with premature immunosenescence and an increased risk of viral infections such as Cytomegalovirus (CMV),^14^ little is known about the immunological consequences of early thymectomy in immunosuppressed transplant patients. In particular, there are no data on the synergetic impact of thymectomy and transplant-related immunosuppression on EBV-specific immunity and the subsequent risk of developing PTLD.

### Study aims and hypothesis

This study aims to investigate the development of EBV-specific immune responses following childhood heart transplant. Specifically, it aims to identify the impact of early thymectomy—compounded by iatrogenic immunosuppression—on EBV immunology and the risk of PTLD.

We hypothesise that a combination of early thymectomy and lifelong immunosuppression therapy establishes a tolerogenic immune profile consisting of dysregulated, exhausted and senescent immune cell subsets, poorly able to control EBV infection. This dysfunctional immune microenvironment permits the uncontrolled proliferation of EBV-infected B-lymphocytes and the subsequent development of PTLD.

## Methods and analysis

### Study design and setting

The Immunology of THymectomy And Childhood CArdiac transplant (ITHACA) study is a prospective nationwide cohort study recruiting children (0–18 years) from the two UK centres currently commissioned to provide paediatric heart transplant services: The Freeman Hospital, Newcastle upon Tyne and Great Ormond Street Hospital for Children, London. The study cohort will consist of 34 prospective heart transplant recipients and a non-thymectomy age-matched control group made up of 6 renal transplant recipients. All patients meeting the study’s eligibility criteria will be identified and recruited through their local transplant teams at the time of listing for cardiac or renal transplantation. The study opened to patient recruitment in March 2022 and is expected to recruit until June 2024.

#### Inclusion criteria

Aged 0–18 years.Actively listed on the National Health Service Blood and Transplant (NHSBT) waiting list for a primary organ transplant or awaiting transplant with a living related donor kidney or recently transplanted with pretransplant blood samples available.Written informed consent.

#### Exclusion criteria

Has a pre-existing diagnosis of an inherited or acquired immunodeficiency.Has an underlying thymic disorder.Has previously received a bone marrow or organ transplant.Has had a previous cancer diagnosis.Withheld consent.Weight under 2.5 kg.

#### Informed consent

Informed consent will be obtained from the parent/carer of the eligible child or from the patient themselves if over the age of 16 years. Assent may be given by children<16 years of age who wish to do so.

A deferred consent approach will be employed for potential study participants who attend a research site’s transplant service for transplantation in a critical/life-threatening clinical situation. This will involve the collection of baseline study samples from potential participants at the point of presurgical workup without written informed consent being received. Discussion about the study, the giving of participant information sheet (PIS) and receiving of written informed consent/assent will be offered at a more appropriate time before further follow-up blood tests are taken. Such cases will require that the clinical team considers obtaining informed consent prior to transplant to be inappropriate. This will be documented in the patient’s clinical notes. Study samples collected under such circumstances will be processed for storage but not analysed until written informed consent is obtained. Any patient who has study samples collected by deferred consent but subsequently declines enrolment in the study will have their samples destroyed in a timely manner according to local laboratory standard operating procedures. Additional consent will be sought to store specimens for future ethically approved research.

#### Assessment and procedures

Children will undergo blood sampling for study-specific investigations during routine clinical visits prior to transplant and at 3, 6, 12 and 24 months post-transplant (figure 1). No additional study-related hospital visits are planned. Medical therapy will be applied as clinically indicated and per the local post-transplantation protocols. A total of 5–20 mL of blood will be taken at each study time point for all participants. This will coincide with their usual transplant-related investigations in adherence to WHO guidance for blood sampling in child health research.^15^ In the case of a prolonged interval between the pretransplant blood sample and subsequent organ transplant (eg, >6 months) additional blood samples will be specifically requested from the patient/parent and verbal consent recorded in the medical record. Relevant clinical data will also be collected from participants at each study time point (online supplemental table 1).

10.1136/bmjopen-2023-079582.supp1Supplementary data

**Figure 1 F1:**
[figure not shown]
Immunology of THymectomy And Childhood CArdiac transplant study flow chart. OHT, orthotopic heart transplant.

Study investigations will consist of:

Immunophenotyping of circulating immune cell subsets.EBV serology.EBV-specific T-lymphocyte quantification.EBV-specific T-lymphocyte functional analysis.

#### Immunophenotyping of circulating immune cell subsets

Circulating immune cell populations will be analysed in Newcastle University laboratories. Mononuclear cells (MNCs) will be isolated and cryopreserved from blood samples taken at each study time point. In addition, biobanked MNC samples from age-matched healthy children will be included for analysis as non-thymectomy, non-transplant controls. Circulating immune cell subsets will be identified within samples using high-dimensional spectral flow cytometry (Aurora system (Cytek)). The 5-laser Aurora spectral cytometer enables an in-depth analysis of up to 40 cell surface markers at a time.^16^ This is highly valuable in phenotypically characterising various immune cell populations and their subsets (including T-lymphocytes, B-lymphocytes, Natural Killer [NK] cells and dendritic cells) in low volume paediatric samples.^17^ These samples will be analysed simultaneously in batches to mitigate interassay variation. A comprehensive list of cell surface markers has been selected to comprise the following:

Major innate/adaptive cell lineages.Main T-lymphocyte subsets as well as putative T-helper subsets.Recent thymic activity.Cellular exhaustion and senescence.Key innate/adaptive cells involved in immune response to EBV infection.

Two full spectrum flow panels have been validated for this purpose. A 24-colour panel has been designed to probe the wider circulating immune landscape of the study cohort (table 1). This is complemented by a targeted 30-colour T-lymphocyte panel that will elucidate any temporal changes in the T-lymphocyte compartment after transplantation (table 2).

**Table 1 T1:** Cell surface markers of interest used in the broad immune full spectrum flow for the Immunology of THymectomy And Childhood CArdiac transplant study

Cell surface marker	Fluorophore	Antibody clone	Purpose
CD45	Spark YG 593	HI03	Leucocytes
TCRγd	PerCP-eFluor 710	B1.1	γd T-lymphocyte
CD3	BV 510	SK7	Pan T-cell, NK T-like cells
CD4	PerCP	SK3	CD4 T-helper lymphocytes
CD8	BUV 805	SK1	CD8 cytotoxic T-lymphocytes
CD11c	PE-Cy7	B-ly6	Dendritic cell differentiation
CD14	Spark Blue 550	63D3	Monocyte differentiation
CD16	BUV 496	3G8	Monocyte, NK cell and dendritic cell differentiation
CD19	Spark NIR 685	HIB19	B lymphocytes
CD20	BV 786	2H7	B lymphocytes
CD21	PE-Cy5	B-ly4	B lymphocyte differentiation
CD24	PE-AF 610	SN3	B lymphocyte differentiation
CD27	APC-H7	M-T271	T/B lymphocyte differentiation
CD38	APC-Fire 810	HIT2	Monocyte, dendritic cell, T/B lymphocyte activation and differentiation
CD56	BUV 737	NCAM16.2	NK cells
CD57	Pacific Blue	NK-1	NK and CD8 T lymphocyte immune senescence
CD123	Super Bright 436	6H6	Plasmacytoid dendritic cells
CD127	APC-R700	HIL-7R-M21	Cytokine receptor; T lymphocyte differentiation
KIR (CD158)	BUV 605	DX27	NK cells
NKG2A (CD159a)	APC	REA110	NK cells
NKG2C (CD159c)	PE	REA205	NK cells
IgD	BV 480	IA6-2	B lymphocyte differentiation
IgM	BV 570	MHM-88	B lymphocyte differentiation
HLA-DR	PE-Fire 810	L243	Monocyte activation, dendritic cell lineage, NK cell lineage discrimination,
Viability	Live/Dead Blue	–	Live cells

NK, Natural Killer.

**Table 2 T2:** Cell surface markers of interest used in the T lymphocyte full spectrum flow panel for the Immunology of THymectomy And Childhood CArdiac transplant study

Cell surface marker	Fluorophore	Antibody clone	Purpose
CD45	Spark YG 593	HI03	Leucocytes
CD45RA	BUV 395	5H9	T lymphocyte differentiation
CD3	BV510	SK7	Pan T-cell, NK T-like cells
CD4	PerCP	SK3	CD4 T-helper lymphocytes
CD8	BUV 805	SK1	CD8 cytotoxic T lymphocytes
TCRγd	PerCP-eFluor 710	B1.1	γd T lymphocyte
CD25	PE-AF700	CD25-3G10	Regulatory T lymphocytes
CD27	APC-H7	M-T271	T lymphocyte differentiation
CD28	BV650	CD28.2	T lymphocyte differentiation
CD31	BV711	WM59	Recent thymic emigrants
CD38	APC-Fire 810	HIT2	T lymphocyte activation/differentiation
CD39	BUV 661	TU66	Regulatory T lymphocytes
CD57	Pacific Blue	NK-1	CD8 T lymphocyte immune senescence
CD62L	BUV 496	SK-11	T lymphocyte differentiation
CD69	AF 647	FN50	T lymphocyte activation
CD95	PE-Cy5	DX2	T lymphocyte activation/differentiation
CD127	APC-R700	HIL-7R-M21	Chemokine receptor; T lymphocyte differentiation
HLA-DR	PE-Fire 810	L243	T lymphocyte activation
CCR4	BB 700	1G1	Chemokine receptor; T lymphocyte differentiation
CCR5	BUV 563	2D7/CCR5	Chemokine receptor; T lymphocyte differentiation
CCR6	BV 480	140 706	Chemokine receptor; T lymphocyte differentiation
CCR7	BV 421	G043H7	T lymphocyte differentiation
CXCR3	AF 488	GH025H7	Chemokine receptor; T lymphocyte differentiation
CXCR5	BV 750	RF8B2	Chemokine receptor; T lymphocyte differentiation
PD-1	BV 785	EH12.2H7	Co-inhibitory receptor; T lymphocyte exhaustion
LAG-3	PE-Cy7	3DS223H	Co-inhibitory receptor; T lymphocyte exhaustion
TIM-3	BV 605	F38-2E2	Co-inhibitory receptor; T lymphocyte exhaustion
CTLA4	PE-CF594	BNI3	Co-inhibitory receptor; T lymphocyte exhaustion
Tetramer (lytic)	APC	–	EBV-specific T lymphocytes
Tetramer (latent)	PE	–	EBV-specific T lymphocytes
Viability	Live/Dead Blue	–	Live cells

EBV, Epstein-Barr virus; NK, Natural Killer.

#### EBV serology

Routine blood samples for evaluation of EBV serology will be tested centrally in the Newcastle upon Tyne NHS Hospitals Foundation Trust (NUTH) virology laboratories. EBV and CMV viral load will be measured from whole blood using PCR assays. Serum and/or plasma will be tested for antibody response to key EBV proteins including IgM/IgG for viral capsid antigen and IgG for EBV Nuclear Antigen 1. The results for viral load assay will be reported as total titres while antibody testing will be reported as a binary detected/not detected based on NUTH laboratories reference cut-off values.

#### EBV-specific T-lymphocyte quantification

An optimised panel of Human Leucocyte Antigen (HLA)-restricted peptide-Major Histocompatibility Complex (pMHC) I/II tetramers will be used to evaluate EBV-specific CD8 and CD4 T-lymphocyte immunity at the time points outlined in figure 1.^18^ This panel will be tailored to maximise coverage of participants who have the most commonly expressed HLA genotypes within our study cohort. Combinations of differently fluorescently labelled pMHC tetramers presenting purified peptides of dominant lytic and latent EBV epitopes,^19^ relevant for the patient HLA genotype, will be included in the T-lymphocyte panel where applicable (table 2). These customised tetramers will be procured from the National Institute of Health Tetramer Core Facility, Atlanta, Georgia, USA.

#### EBV-specific T-lymphocyte functional analysis

To assess the functional capacity of EBV-specific T-lymphocytes in an HLA-unbiased manner, effector cytokine production of interferon gamma will be determined by ELISpot following stimulation with pools of overlapping peptides (JPT PepMix) representing the full sequences of a panel of EBV latent and lytic cycle proteins.^20 21^

#### Data collection

Study data will be collated and managed using Research Electronic Data Capture (REDCap) electronic case report forms.^22^ REDCap is a secure, web-based platform specifically designed to support data acquisition for research studies. It provides restricted user rights to protect identifiable data, including audit trails for tracking data handling and export and procedures for data integration with external sources.^23^

### Outcome measures

Primary outcomes measures:

Proportions of circulating innate and adaptive immune cell subsets before and at 3, 6, 12 and 24 months post-transplant.Frequency of detectable EBV-specific T-lymphocyte immunity.Functional capacity of EBV-specific T-lymphocytes.

Secondary outcome measures:

Incidence of EBV infection.Time from transplantation to EBV viraemia.Time from EBV viraemia to seroconversion.

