### Statistical analysis

Data from spectral flow cytometry will be analysed using the OMIQ platform (https://www.omiq.ai/). Automated clustering and dimensionality reduction will be used to identify immune cell populations by FlowSOM and Uniform Manifold Approximation and Projection, respectively. These techniques overcome the practical challenges associated with manual gating and user bias when analysing datasets from large flow panels.

Statistically different immune signatures between patients with early thymectomy and late or non-thymectomy, EBV+ and EBV− serostatus and between time points, will be identified by linear and generalised linear mixed models (statistical significance defined as p<0.05). Continuous variables will be assessed by Pearson correlation using the single linkage method to group patients by expression values, and non-continuous variables by non-parametric Spearman correlation, as appropriate. Viral loads will be serially quantified at each study time point to correlate changes in immune responses with the volume of circulating virus-infected cells. Tetrameric frequencies for population groups (eg, early vs late/non-thymectomy) will be compared using Mann-Whitney U test and between time points for paired patient sample using Wilcoxon signed-rank test.

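### EBV PCR and antibodies are described only on a 0, 3, 6, 12 and 24 month grid, too coarse to time the lag from viraemia to seroconversion

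*Protocol article*

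**What the plan says.** Two of the three secondary outcomes under Outcome measures are durations: time from transplantation to EBV viraemia, and "Time from EBV viraemia to seroconversion".

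Assessment and procedures places blood sampling "during routine clinical visits prior to transplant and at 3, 6, 12 and 24 months post-transplant", and adds: "No additional study-related hospital visits are planned". The abstract says that EBV-specific T-cell function, "along with EBV antibodies and viral load will be monitored at each of the predefined study time points". The Statistical analysis section repeats this for PCR: "Viral loads will be serially quantified at each study time point".

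Under EBV serology, "EBV and CMV viral load will be measured from whole blood using PCR assays", while "antibody testing will be reported as a binary detected/not detected based on NUTH laboratories reference cut-off values". The same section describes the tested material as routine blood samples. Clinical data are collected at each study time point, and their content is listed in a supplement that is not shown.

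**The concern.** A duration between two events can be measured no more finely than the events are dated. Here both events are seen on the same sparse grid, with post-transplant gaps of 3, 3, 6 and 12 months. Antibody is read as present or absent, so no titre helps to place seroconversion within a gap.

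The problem is sharper for the lag than for time to viraemia. Time to viraemia runs from a known date (transplantation) to one interval-censored event. The lag is the difference of two interval-censored events, often censored in the same interval. If the true lag is short compared with the gaps, the recorded value depends largely on where the visits fall. The study sets out to describe how the immune response to EBV unfolds over time, so a lag reported at face value could mislead even in a descriptive study.

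**Working it through.** The article states no figure for these outcomes, so there is none to reproduce.

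**Step 1: possible recorded values.** Each event is assigned to the first visit at or after it occurs.

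- First viraemia at 3 months: lag 0, 3, 9 or 21 (seroconversion seen at 3, 6, 12 or 24).
- First viraemia at 6 months: lag 0, 6 or 18.
- First viraemia at 12 months: lag 0 or 12.
- First viraemia at 24 months: lag 0 or censored.

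A completed lag is therefore 0, 3, 6, 9, 12, 18 or 21 months. The same true lag of 1 month is recorded as 0 if it runs from month 1 to 2, as 3 if from 2.5 to 3.5, as 6 if from 5.5 to 6.5, and as 12 if from 11.5 to 12.5. This step needs no assumption about EBV.

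**Step 2: how often the two events share a visit.** The article gives neither the onset nor the lag distribution, so both are assumed:

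- onset exponential, median 6 or 12 months (rate λ = ln 2 / median);
- lag exponential, median 1 to 9 months (rate μ = ln 2 / median);
- seroconversion not before viraemia, and viraemia and antibody still detectable at the next visit.

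For a gap from a to b, the probability that onset falls in it is e^(−λa) − e^(−λb). The probability that both events fall in it is

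[e^(−λa) − e^(−λb)] − λ/(μ−λ) × [e^(−λb) − e^(−λa−μ(b−a))].

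Worked case, onset median 6 and lag median 1, so λ/(μ−λ) = 0.2:

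- 0–3 months: 0.2929 − 0.2 × (0.7071 − 0.1250) = 0.1765
- 3–6 months: 0.2071 − 0.2 × (0.5000 − 0.0884) = 0.1248
- 6–12 months: 0.2500 − 0.2 × (0.2500 − 0.0078) = 0.2016
- 12–24 months: 0.1875 − 0.2 × (0.0625 − 0.0001) = 0.1750

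The sum is 0.678. The probability of onset by 24 months is 1 − 2^(−4) = 0.9375. The share is 0.678 / 0.9375 = 72%.

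The same calculation in the other settings, as a share of children with detected viraemia, agrees with simulation (400,000 draws per setting):

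| Median lag (months) | Onset median 6 | Onset median 12 |
|---|---|---|
| 1 | 72% | 75% |
| 2 | 55% | 59% |
| 3 | 44% | 48% |
| 6 | 28% | 31% |
| 9 | 20% | 23% |

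**Step 3: other shapes.** With onset also uniform over 0–12 or 0–24 months, and the lag either fixed or exponential, zeros make up 67–87% of completed lags for a 1-month lag, 25–63% for 3 months and 0–51% for 6 months. These shares leave out lags still open at 24 months, so they are not directly comparable with the table.

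**Step 4: delay in dating viraemia.** Under the exponential onsets the median delay is 2.3 months (onset median 6) or 2.6 months (onset median 12), and the mean is 3.2 or 3.7 months. The mean is pulled up by the 12–24 month gap, where the delay averages about 7 months. For viraemia first seen by month 12 it averages about 2.2 months.

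**The case against.** The strongest reply is that the article never says study samples are the only source. It says the assays are done at each time point, that routine blood samples are tested, and that sampling coincides with the usual transplant investigations. The list of clinical data is in a supplement not shown. Interim PCR results may therefore already be captured. This stands, and it makes the point conditional: the article as written ties both measures to the study time points, and one sentence from the sponsor could settle the matter.

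It can also be said that interval censoring and the definition of the risk set belong in an analysis plan. That stands too. Their absence from an article is not counted as a fault. The risk set can be formed from planned data, since a pre-transplant sample is taken and the Statistical analysis section already separates EBV+ from EBV− serostatus. What remains is the mismatch between a stated outcome and a stated sampling grid, and no analysis recovers timing within a gap.

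A reader might infer four stronger things that the document does not support.

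- *Most lags will be recorded as zero.* This holds only for short lags. At a median of 3 months the share is already below half, and the article gives no lag.
- *Both times merely reflect the visit calendar.* Time to viraemia still sorts children into four intervals and remains informative.
- *The early versus late thymectomy comparison of these times is lost.* The Statistical analysis section compares those groups on immune signatures and tetramer frequencies, and states no such test for either time.
- *Maternal antibody in infants puts children in the wrong risk set.* The article does not mention maternal antibody, so this would rest on outside knowledge. It also lists IgM, two IgG targets and PCR, not a single IgG result.

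**Conclusion.** The concern holds in limited form. If study samples are the only source, the viraemia-to-seroconversion lag is confined to seven values set by the visit schedule, and this needs no assumption. How often the recorded value is zero depends on quantities the article does not give: about three quarters of children with detected viraemia for a 1-month median lag, under half for 3 months, and a fifth to just under a third for 6–9 months. These shares assume exponential onset with median 6 or 12 months and events that stay detectable until the next visit. Time to viraemia is dated late by a median of roughly two and a half months, but can be analysed as interval-censored. The point affects secondary outcomes only, since none of the primary outcomes is a time to event. It falls away in part if interim routine results are already collected with dates.

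**What to change.** 1. State whether EBV PCR and serology results from routine care between study visits are captured. If not, add REDCap fields for their dates and results, and use them together with the study samples to date first viraemia and seroconversion.
2. Analyse time to viraemia as interval-censored, with the Turnbull estimator or a discrete-time complementary log-log model by visit interval, among children who are EBV PCR-negative and seronegative before transplant.
3. If the lag still cannot be resolved, replace it with seroconversion by the next study visit after first viraemia. Report this by the visit of first viraemia, because the next visit lies 3, 6 or 12 months later, and a child first viraemic at 24 months has none.

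The cost is extra data fields and a changed outcome definition, with no additional samples or visits. The drawback is that the frequency of routine testing may differ between centres, so interval widths would differ too. An interval-censored analysis can carry unequal widths, but testing frequency by centre should be reported.
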